#### Secondary endpoints

PCR unadjusted treatment failure up to day 63 (TF63U); Time to treatment failure (PCR adjusted and unadjusted) during 63 days of active follow-up after treatment; Asexual parasite clearance time (PCT): Asexual parasite clearance time is defined as the time (in days) from time of randomization to 2 consecutive negative blood slides (collected at different days) - the time to the event is taken as the time to the first negative slide; Gametocytaemia (prevalence and density) at day 7, 14, 21, 28 and 63 after treatment; Hb changes day 14, 28, 42 and 63; Acute, chronic or past infection of the placenta (prevalence); Mean birth weight and prevalence of low birth weight.

#### Laboratory procedures

##### Haematology

Maternal haemoglobin is measured using Hb301 Hemocue*®*, Angelholm, Sweden, according to manufacturer’s instructions.

##### Peripheral malaria infection

Blood samples are collected by finger prick at specified time points during the trial for blood slides (thick blood film) and blood spots on filter paper. Thick blood smears are stained with 3% Giemsa for 30 minutes and read by trained microscopists at each site. Parasite densities are calculated by counting the number of asexual parasites per 200 leukocytes (or per 500 leukocytes if the count is <10 asexual parasites/200 leukocytes), assuming a leukocyte count of 8,000/μl. A blood smear is considered negative when the examination of 100 high power fields does not reveal asexual parasites. Each slide is read separately by two experienced microscopists and discrepancies resolved by a third reader.

Blood spots on filter paper are used for genotyping recurrent malaria infections during follow up and compared them with pre-treatment samples. This is done by characterizing MSP1, MSP2 and GLURP, single-copy genes in the *Plasmodium falciparum* genome. For the three genes, each PCR-amplification product of a different size is considered to originate from a different clone of *Plasmodium falciparum*, reflecting a different genotype. For the samples collected from the same patient at day 0 and day of recurrent parasitaemia, the length polymorphism of MSP1, MSP2 and GLURP are determined, i.e. the number of bands in each PCR reaction and their respective size. Results are interpreted as follows:

Recrudescence: For each marker (MSP1, MSP2 and GLURP), at least one identical length polymorphism is found in the sample collected at day 0 and day of recurrent parasitaemia.New infection: For at least one marker, length polymorphism is different between the sample collected at day 0 and that at day of recurrent parasitaemia.Indeterminate: Samples that fail to produce a result due to an inability to amplify DNA at day 0 and/or day of recurrent parasitaemia.

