#### Primary endpoint

There are two primary end points:**Treatment Failure** (TF) (PCR adjusted) at day 63 defined according to the WHO criteria [14] as the sum of early and late treatment failures. Early Treatment Failure (ETF) could be one of the following: Development of danger signs or severe malaria on Day 0, Day 1, Day 2 or Day 3, in the presence of parasitaemia; Parasite density on Day 2 > Day 0 count, irrespective of axillary temperature; Presence of parasitaemia on Day 3 with fever (axillary temperature ≥ 37.5°C); Parasitaemia on Day 3 ≥ 25% of count on Day 0. Late treatment failure (LTF) is divided in late clinical and late parasitological failure. Late Clinical Failure (LCF): Development of danger signs or severe malaria on any day after Day 3 in the presence of parasitaemia, without previously meeting any of the criteria of Early Treatment Failure; Presence of parasitaemia and fever on any day after Day 3, without having previously meet the criteria of ETF. Late Parasitological Failure (LPF): Presence of parasitaemia on any day from day 7 onwards and axillary temperature <37.5°C, without previously meeting any of the criteria of ETF or LCF. The Adequate Clinical and Parasitological Response (ACPR) is 1-TF. It is defined as absence of parasitaemia at the end of the follow up period, irrespective of axillary temperature without previously meeting any of the criteria of early and late treatment failure. In the adjusted estimates, patients with late asexual parasite reappearance (with or without fever) are considered ACPR if the PCR analysis shows a new infection rather than a recrudescence.**Safety profiles** including significant changes in relevant laboratory values. Subjects are monitored for 63 days for possible development of adverse events. All adverse events are recorded on the specific form in the electronic CRF. Vital signs, blood chemistry and haematology are monitored and changes in relevant laboratory parameters are assessed.

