#### Sample size

The sample size for this study was determined by simulation with the following assumptions and requirements: (1) study conclusions are determined by two-sided 95% confidence intervals for difference in response rates (% of therapeutic success), with decision rule as described below, (2) all 4 treatments have identical true response rates of 95%, (3) 95% power for each of the 6 pair-wise comparisons and 80% power for the combined hypothesis that all treatments are therapeutically equivalent is required. With these assumptions, approximately 700 patients/treatment arm are needed. If the true response rate for one of the treatments is lower than 95%, then power is reduced to 80% (for a true response rate of 94%) or 50% (for a true response rate of 93%). Allowing for a 20% loss to follow-up, a total of 870 patients are recruited to each treatment; this is equivalent to 290 patients in each treatment group in each centre (i.e. a total centre sample size of 870 patients) – and hence a total study sample size of 3480 patients. Inclusion of HIV-infected women is not expected to have a major influence on the sample size calculation. The percentage of therapeutic success may be slightly but not dramatically lower in this subgroup of patients.

For safety, when combined, the trial is able to detect with 90% power major adverse events occurring at the frequency of at least 2-3%.

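### The PCR rules for recrudescence and new infection overlap in multi-clone infections, with no precedence, although the class decides failure or cure on the primary endpoint

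*Protocol article*

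**What the plan says.** All the genotyping rules are in the protocol article under Laboratory procedures, Peripheral malaria infection.

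- Several clones per sample are foreseen: "each PCR-amplification product of a different size is considered to originate from a different clone".
- What is determined for each marker is its length polymorphism, "i.e. the number of bands in each PCR reaction and their respective size".
- Recrudescence: "For each marker (MSP1, MSP2 and GLURP), at least one identical length polymorphism is found in the sample collected at day 0" and again in the recurrence sample.
- New infection: "For at least one marker, length polymorphism is different between the sample collected at day 0 and that at day of recurrent parasitaemia".
- Indeterminate: "Samples that fail to produce a result due to an inability to amplify DNA at day 0 and/or day of recurrent parasitaemia".

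Under Primary endpoint, women whose parasites reappear late "are considered ACPR if the PCR analysis shows a new infection rather than a recrudescence". A late recrudescence therefore remains a treatment failure. The same classes feed the PCR-adjusted time to failure (Secondary endpoints) and the choice of day 7 samples (PK assessment). The list of safeguards under Study design states that PCR interpretation is blinded to allocation.

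**The concern.** The first rule asks whether each marker has something in common between the two samples. The second asks whether some marker has something different. With one band per marker these are opposites. With several bands they are not, because two band profiles can share a band and still differ. The section's own description of length polymorphism, as band number and sizes, makes a gained or lost band a difference.

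A pair caught by both rules can be scored as failure or as cure, and the text does not say which comes first. The class feeds the PCR-adjusted primary endpoint of a trial whose conclusion is equivalence. A rule that moves late failures into the cure class in every arm would make treatments look more alike, and blinding does not prevent that.

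**Working it through.** **1. One pair against both rules.** Take MSP1 bands {a,b} at day 0 and {a,c} at recurrence, with MSP2 and GLURP identical in the two samples.

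- Recrudescence rule: MSP1 shares a, and MSP2 and GLURP match. Met.
- New-infection rule as written: the MSP1 profile differs. Met.
- Indeterminate: all samples amplified. Not met.
- New infection reworded as no common band at one or more markers: MSP1 shares a. Not met.

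**2. How far the overlap reaches as a matter of logic.** Allow up to three band sizes at each of the three markers.

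- Non-empty band sets per marker: 2³ − 1 = 7, so 7 × 7 = 49 ordered day 0/recurrence pairs.
- Pairs with no band in common: 3³ − 2 × 2³ + 1 = 12, so 49 − 12 = 37 share a band. Identical pairs: 7.
- All three markers: 49³ = 117,649 combinations.
- Recrudescence rule met: 37³ = 50,653.
- Of these, identical at every marker: 7³ = 343.
- Both rules met: 50,653 − 343 = 50,310.
- One band per marker in both samples: every sharing pair is identical, so the overlap is 0.
- Reworded rule: new infection takes 117,649 − 50,653 = 66,996 combinations, the overlap is 0, and every amplified pair falls in exactly one class.

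These are unweighted counts of possibilities. They say nothing about how often such pairs occur.

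**3. The plan's own power, as background.** The point challenges no stated figure. Inputs from Sample size and Efficacy: 95% response, margin ±5 points, two-sided 95% interval, about 700 evaluable per arm. Design efficiency, with four treatments, three per centre, each treatment in three centres and each pair together in two: (2 × 4)/(3 × 3) = 8/9.

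- SE = √[2 × 0.95 × 0.05 / (700 × 8/9)] = 0.01236.
- Power = 2Φ(0.05/0.01236 − 1.96) − 1 = 96.3%, against 95% stated. The stated power is met.

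**4. Direction of effect under a literal new-infection rule.** Let E be early failure, L true late recrudescence, and q the share of late recrudescences that show a gained or lost band. Then

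PCR-adjusted failure as read = E + L(1 − q).

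The document gives no value for q, so the range below is an assumption. For illustration, take 5% against 10% true failure, all of it late, the same q in both arms, and 700 per arm.

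| q | Failure as read | Difference | 95% CI, simple | 95% CI, efficiency 8/9 |
|---|---|---|---|---|
| 30% | 3.5% v 7.0% | 3.5 | 1.2 to 5.8 | 1.0 to 6.0 |
| 60% | 2.0% v 4.0% | 2.0 | 0.2 to 3.8 | 0.1 to 3.9 |

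The simple SE at q = 30% is √[(0.035 × 0.965 + 0.07 × 0.93)/700] = 0.0119. At q = 60% it is √[(0.02 × 0.98 + 0.04 × 0.96)/700] = 0.0091. The other column divides each by √(8/9).

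Under the Efficacy decision rule the whole interval must lie within ±5%. At q = 30% it contains 5, so equivalence is not concluded. At q = 60% it lies inside. Any early failure makes the shrinkage smaller.

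**The case against.** The best answer is that the two rules were meant as complements. In the recrudescence rule the term is countable: "at least one identical length polymorphism is found in the sample collected at day 0 and day of recurrent parasitaemia" refers to one band size, not the whole profile. In that sense, a marker that is different is one with no identical band, and the rules are exact opposites. The literal reading also nearly empties the first rule, since only 343 of 50,653 qualifying combinations would escape the second. Primary endpoint and PK assessment both treat the classes as exclusive. This is probably what was intended. But the text does not state it, and the section's own description of length polymorphism points the other way.

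A second objection is that band-matching detail belongs in a laboratory manual and may be left out of an article. That would answer an omission. Here the interpretation rules are set out, and as worded they conflict.

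Three limits stand in full. PCR interpretation is blinded to allocation, so inconsistent scoring should not by itself favour an arm. Early failures are not PCR-adjusted. The PCR-unadjusted secondary endpoint does not use the rule.

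**Conclusion.** The concern holds as a badly stated rule. Multi-clone pairs that share a band at every marker and differ at one or more of them meet both definitions, and nothing decides between them. That follows from the text alone and needs no assumption.

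The size of the effect is unknown. The document gives neither the share of recurrences with several clones nor the share with gained or lost bands. The direction is clear only under a literal new-infection rule: late failure falls in all arms, and differences shrink if q is similar between arms.

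A reader might infer that the overlap would hide a true 5-point difference, or that most recrudescences are misclassified. The document supports neither. The first depends on an assumed q and on comparing a point difference with the margin, whereas "study conclusions are determined by two-sided 95% confidence intervals for difference in response rates"; at q = 30% equivalence would not be concluded. The second mistakes a count of logical possibilities for a frequency. Nor does anything show that the laboratory applied the literal reading.

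**What to change.** Reword the second class: *New infection: for at least one marker, no band size is common to the day 0 and recurrence samples.* Add that extra or missing bands do not change a recrudescence when every marker shares a band.

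Trial status says that data collection is complete, so also confirm that all recurrent pairs, at all sites, were classified by this rule. Where they were not, re-classify them from the recorded bands, keeping the blinding to allocation that is already in place.

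The cost is one or two sentences and, at most, a re-reading of band data that the trial already determines. No new samples or assays are needed.

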##### Placental malaria

A 1 cm^3^ biopsy specimen is obtained from the maternal-facing side of the placenta as soon as possible after delivery. Biopsy specimens are preserved in 10% neutral buffered formalin which are processed and embedded in paraffin wax by standard techniques. Pending histological evaluation, all biopsies are kept at 4°C. Paraffin sections 4 mm thick are stained with haematoxylin-eosin stain.

Placental biopsies are classified according to the following definitions [15]:Acute infection (parasite present, malaria pigment absent)Chronic infection (parasites and malaria pigment present)Past infection (no parasite but pigment present)No infection (both parasites and malaria pigment absent)

##### PK assessment

Individual pharmacokinetic studies are often underpowered for identifying the factors that influence antimalarial pharmacokinetic parameters, which may have a major influence on the observed therapeutic response. Complementing efficacy data with some information on the pharmacokinetic properties of the treatment used allows a better interpretation of the observed recurrent infections or true recrudescences/new infections, as these may be the results of inadequate drug levels because of altered distribution, poor absorption or metabolism. The day 7 drug concentration has been shown to be the most important single measure, in terms of correlation with the area under the concentration time curve and association with treatment response, for lumefantrine, piperaquine and mefloquine [16]. Therefore, a blood sample of 2 ml is collected from all women at day 7 with the aim of measuring with an appropriate assay the concentration of the partner drug to the artemisinin derivative. Not all samples will be analysed; instead a smaller number of samples will be chosen for the analysis according to the observed therapeutic response, i.e. in each arm women having experienced a true recrudescence will be compared with those having had a new infection and with those with an adequate clinical and parasitological response. Analysis of the blood samples will be carried out within the Malaria in Pregnancy Consortium.

##### In-vitro tests

This component is carried out at the sites in Burkina Faso only. The sensitivity of the parasites to the drugs used is determined by carrying out *in vitro* tests. Venous blood samples (5 ml) are collected at day 0 before treatment from women with a parasite density of at least 4,000/μL. The HRP2 ELISA [17, 18] is used to measure the proliferation of *P. falciparum* in the presence of lumefantrine, monodesethylamodiaquine (active metabolite of amodiaquine), mefloquine, piperaquine and dihydroartemisinin (active metabolite of artemisinin derivatives).

#### Sample size

The sample size for this study was determined by simulation with the following assumptions and requirements: (1) study conclusions are determined by two-sided 95% confidence intervals for difference in response rates (% of therapeutic success), with decision rule as described below, (2) all 4 treatments have identical true response rates of 95%, (3) 95% power for each of the 6 pair-wise comparisons and 80% power for the combined hypothesis that all treatments are therapeutically equivalent is required. With these assumptions, approximately 700 patients/treatment arm are needed. If the true response rate for one of the treatments is lower than 95%, then power is reduced to 80% (for a true response rate of 94%) or 50% (for a true response rate of 93%). Allowing for a 20% loss to follow-up, a total of 870 patients are recruited to each treatment; this is equivalent to 290 patients in each treatment group in each centre (i.e. a total centre sample size of 870 patients) – and hence a total study sample size of 3480 patients. Inclusion of HIV-infected women is not expected to have a major influence on the sample size calculation. The percentage of therapeutic success may be slightly but not dramatically lower in this subgroup of patients.

For safety, when combined, the trial is able to detect with 90% power major adverse events occurring at the frequency of at least 2-3%.

#### Statistical analysis

A detailed analysis plan is drawn up prior to the analysis.**Baseline comparability**: Patients in each treatment group in each site are described separately with respect to baseline characteristics. The clinical importance of any imbalance will be noted, though statistical tests of significance are not undertaken.**Primary analyses**: The primary analysis of the study is the assessment of therapeutic equivalence of the 4 treatments (clinical non-inferiority) with respect to therapeutic success at day 63 and their safety throughout the follow-up, i.e. up to one year after delivery.

##### Efficacy

Therapeutic equivalence is assessed using the pair-wise difference in response rates (percentage of women with therapeutic success). Assessment of the difference in true response rates is performed by calculating the two-sided 95% confidence interval for the difference in response rates from the observed data, using the following decision rule:

if the two-sided 95% confidence interval for the difference in response rates lies entirely between −5% and +5%, then therapeutic equivalence of the two treatments is concluded;if the 95% confidence interval for the difference in response rates includes −5% or +5%, then therapeutic equivalence cannot be established;if the 95% confidence interval for the difference in response rates lies entirely below −5% or entirely above 5%, then one treatment is clinically inferior to the other.

The primary analysis uses the combined data from all 4 centres together, with adjustment for any centre effects, using an additive model for the response rates (i.e. a generalized linear model with Bernoulli error distribution and an identity link function). This allows the assessment of all 6 possible pair-wise treatment comparisons using all available data. Equivalence will be established using two-sided confidence intervals. Though 6 treatment comparisons will be performed, no adjustment for multiplicity is needed as the focus of the study is on the individual pair-wise treatment comparisons. In addition, combined hypotheses of interest (e.g. all 4 treatments are therapeutically equivalent) require each of the individual hypotheses to be accepted. Consequently, there is no inflation of the type I error rate due to multiple testing. However, the power for combined hypotheses is lower than for the individual pair-wise comparisons. Thus, the power calculation of this study required a high (95%) power for individual pair-wise treatment comparisons, resulting in an acceptable (80%) power for the combined hypothesis. For the efficacy analysis, both an intention-to-treat and a per-protocol approach are adopted, with the per-protocol analysis being the primary approach, as recommended for equivalence studies.

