### Trial objectives and purpose

The main objective of the trial is to determine the safety and efficacy of 4 ACTs when administered to pregnant women with *P. falciparum* infection during the second and the third trimester, and collect explanatory variables for therapeutic response. The primary hypothesis is the clinical equivalence (pair-wise non-inferiority) of the 4 treatment regimens, with clinical equivalence defined as difference in treatment failure rates (PCR corrected) of 5% or less.

Specific objectives are:

to compare the efficacy of AL, AQ-AS, MQ-AS and DHA-PQ in terms of treatment failure by 63 days after start of treatment with or without genotyping; Parasite clearance time; Haematological recovery by 14, 28, 42 and 63 days post-treatment and at delivery; Birth weight measured within 72 hours of delivery; and prevalence of placenta *P. falciparum* malaria;to describe the safety profile of AL, AQ-AS, MQ-AS and DHA-PQ in terms of tolerability; incidence of adverse events until one year post-partum;to determine the relation between drug pharmacokinetics (Day 7 levels of the partner drug) and response to treatment;to assess the *in vitro* susceptibility of *P. falciparum* isolates collected before treatment to several drugs, including the partner drug tested, and to correlate their IC_50_ to treatment response.

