### Trial design

#### Study design

This is a non-inferiority, multicentre, randomized, open label study on 4 antimalarial treatments, namely DHA-PQ, MQAS, AQAS and AL, assessed in each site using a “balanced incomplete block design” – with 3 out of 4 arms used in each site. There are 7 sites in the study distributed in the four countries, i.e. Burkina Faso (Nanoro and Nazoanga), Ghana (Effiduase, Ejisu and Juaben), Malawi (Chikwawa) and Zambia (Nchelenge).

The treatments tested are distributed in a way to allow a head-to-head comparison and the establishment of the treatment’s relative value according to a series of outcomes (Table 1). This approach has the advantage of testing several treatment options at the same time, maximizing the use of resources, and is the most likely to achieve our aim of identifying at least 2 antimalarial treatments suitable for use in pregnancy and one rescue/alternative treatment.

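### The decision rule of this non-inferiority trial has no one-directional conclusion: an interval that excludes −5 but includes +5 points is reported only as equivalence not established

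*Protocol article*

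**What the plan says.** Study design gives the label: "This is a non-inferiority, multicentre, randomized, open label study on 4 antimalarial treatments". The design paragraph of the Abstract uses the same term.

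The hypothesis and the primary analysis are worded as equivalence, with non-inferiority in brackets. Trial objectives and purpose: "The primary hypothesis is the clinical equivalence (pair-wise non-inferiority) of the 4 treatment regimens". Statistical analysis: "the assessment of therapeutic equivalence of the 4 treatments (clinical non-inferiority) with respect to therapeutic success at day 63".

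Efficacy fixes the rule. Each pair is judged by "calculating the two-sided 95% confidence interval for the difference in response rates from the observed data", with three outcomes:

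- the interval "lies entirely between −5% and +5%, then therapeutic equivalence of the two treatments is concluded";
- the interval contains either limit, −5 or +5 points: "then therapeutic equivalence cannot be established";
- the interval lies wholly outside ±5 points on one side, and one treatment is then called clinically inferior.

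Sample size bases study conclusions on this rule and requires 95% power for each pair and 80% for all six pairs together. Study design gives the practical aim as "identifying at least 2 antimalarial treatments suitable for use in pregnancy", plus one rescue or alternative treatment. Table 1 names a comparator for each region.

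**The concern.** Non-inferiority is a directional claim: A is not worse than B by more than the margin. Take an interval for A minus B of +2 to +8 points. It rules out that A is worse than B by 5 points or more. It also includes +5, so it falls into the second outcome, where the rule says only that equivalence was not shown. No outcome lets the trial state that A is non-inferior to B.

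The stated aim is to find suitable regimens and to rank their relative value against named comparators. A pair in which one regimen is moderately better bears directly on that aim, and it is the kind of pair most likely to end in the second outcome. If the directional reading is added only after the results of an open-label trial are known, it will look post hoc even though the interval supports it.

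**Working it through.** **Inputs**

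- Margin 5 points and two-sided 95% interval, so z = 1.96 (Efficacy).
- 870 women recruited per regimen with 20% loss (Sample size): 870 × 0.8 = 696 evaluable.
- Four countries with three of the four regimens in each (Table 1). Each regimen appears in 3 countries and each pair together in 2, so the efficiency of the incomplete block design is (2 × 4)/(3 × 3) = 8/9. Effective number per regimen: 696 × 8/9 = 618.7.
- True rates: 95%, 94% and 93% are in Sample size. Background and rationale gives 90–95% for AQ-AS and usually above 95% for the other three. All other rates below are assumptions.

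**Formulas**, with d = pA − pB and A the better regimen

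- SE = √[(pA(1−pA) + pB(1−pB))/618.7]
- P(equivalent) = Φ((0.05−d)/SE − 1.96) − Φ((−0.05−d)/SE + 1.96)
- P(B clinically inferior) = 1 − Φ((0.05−d)/SE + 1.96)
- P(not established) = 1 minus the two above
- P(A shown non-inferior) = Φ((0.05+d)/SE − 1.96)

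**Step 1: the plan's own power.** At 95% in both arms, SE = √(2 × 0.95 × 0.05/618.7) = 0.01239. Then 0.05/0.01239 − 1.96 = 2.075, and power = 2Φ(2.075) − 1 = 96.2%, against 95% required. A simulation of the additive identity-link model with 700 per regimen gave 96.1–96.5% per pair and 84.5% for all six, against 80% required. The sample size therefore fits the two-sided rule.

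The reduced powers stated for one regimen at 94% or 93% (80% and 50%) do not reproduce as closely. The formula gives 87% and 60% per pair; the simulation gives 69% and 38% for all six. The protocol does not say which hypothesis they refer to, and nothing below rests on them.

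**Step 2: what the rule says for given observed rates**

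- 98% vs 96%: interval +0.1 to +3.9, equivalent.
- 98% vs 93%: interval +2.7 to +7.3, not established, although −5 is far outside.
- 98% vs 90%: interval +5.4 to +10.6, the second regimen clinically inferior.

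**Step 3: how often each outcome occurs**

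| True rates, A vs B | Equivalent | Not established | B clinically inferior | A shown non-inferior |
|---|---|---|---|---|
| 95 vs 95 | 96% | 4% | 0% | 98% |
| 95 vs 94 | 87% | 13% | 0% | 99.6% |
| 95 vs 93 | 60% | 40% | 0% | 99.9% |
| 95 vs 92 | 30% | 70% | <0.1% | about 100% |
| 95 vs 90 | 2.5% | 95% | 2.5% | about 100% |
| 98 vs 96 | 87% | 13% | 0% | about 100% |
| 98 vs 95 | 48% | 52% | <0.1% | about 100% |
| 98 vs 93 | 2.5% | 95% | 2.5% | about 100% |
| 98 vs 92 | 0.3% | 87% | 13% | about 100% |
| 98 vs 90 | 0% | 38% | 62% | about 100% |
| 98 vs 88 | 0% | 6% | 94% | about 100% |

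The simulation at 700 per regimen agrees: not established in 51% at 98 vs 95, 95% at 98 vs 93, 87% at 98 vs 92 and 37% at 98 vs 90.

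**Step 4: what a second-outcome interval contains.** The full width is 2 × 1.96 × SE: 4.9 points at 95 vs 95 and 5.8 points at 95 vs 90. An interval must be at least 10 points wide to contain both limits. At the planned size, an interval that includes one limit therefore excludes the other, so practically every result in the second outcome already shows non-inferiority in one direction.

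**The case against.** Three points can be made for the plan.

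- **The rule matches its hypothesis.** The hypothesis is equivalence, the sample size is built on the two-sided rule, and the per-protocol set is justified by reference to equivalence studies. Two-sided equivalence is a coherent choice for four active regimens compared pair by pair. This stands. A reader might infer that the rule contradicts the hypothesis or the power calculation, but step 1 shows that it does not. The defect is a missing directional conclusion under a non-inferiority label.
- **The protocol expects about 95% in every arm.** Under that expectation the second outcome is rare (4%), and the only departures it considers are 94% and 93%. This also stands and limits the size: 13% and 40% come from the document's own rates, while 95% needs a 5-point difference that is assumed. The 90–95% range quoted for AQ-AS shows that such a difference is not far-fetched.
- **Nothing forbids interpreting the interval.** The second outcome is literally true, the interval will presumably be reported, and the analysis plan, not shown here, may say how to read it. This lowers the severity. The gap remains, because Sample size says the written rule determines the study conclusions, and that rule has no such outcome.

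A reader might also infer that a clearly better regimen always ends as not established and can never be called non-inferior. The text does not support this. An interval inside ±5 gives equivalence, which the protocol itself equates with pair-wise non-inferiority: 87% of trials at 98 vs 96. An interval wholly beyond +5 names the other regimen clinically inferior: 62% at 98 vs 90.

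**Conclusion.** The concern holds as a gap in the conclusions the rule can reach. It does not show an invalid test: the estimate, interval, equivalence rule and sample size are unaffected. The gap matters mainly for true differences of roughly 2 to 6 points and fades beyond that (38% at 98 vs 90, 6% at 98 vs 88). Within it, between about one trial in eight and nineteen in twenty would report only that equivalence was not established, while the data show almost with certainty that the better regimen is non-inferior.

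These figures assume 696 evaluable women per regimen spread evenly over the Table 1 cells, the normal approximation, and the listed true rates.

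A reader might also conclude that superiority can be read from the same interval at no cost. Within one pair that is so. Across six pairs with all four regimens truly equal, the chance of at least one lower limit above 0 for the better-looking regimen is about 20% (range of four means, normal approximation). The multiplicity argument under Efficacy rests on individual pairs and on combined hypotheses that need every pair to pass. It does not cover claiming superiority for whichever pair shows it.

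Severity: a free or cheap improvement, not a mandatory correction.

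**What to change.** Keep equivalence as the primary hypothesis, and keep the first and third outcomes as written. Add to the rule under Efficacy, or to the analysis plan before analysis, that for each ordered pair A is declared non-inferior to B if the lower limit of the same two-sided 95% interval for A minus B is above −5 points, and that equivalence is concluded when this holds in both directions. The second outcome would then report which direction, if any, was shown.

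Within a pair at most one direction can be truly inferior by the margin or more, so the error of the added claim is 2.5% per pair. This is the same per-side level as the existing rule, under its existing focus on individual pairs.

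If a superiority reading (lower limit above 0) is wanted, label it secondary and either adjust it for the six comparisons or report it explicitly as unadjusted.

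Cost: a short paragraph, with no extra patients or data. Trial status says data collection is complete, so the wording should be dated and fixed before the comparative results are examined.
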